# STUDY IMPLEMENTATION

An inclusion visit and two follow-up visits are planned. Patient inclusion and follow-up will take place at the patients’ usual treatment centres.

## ASSESSMENT SCHEDULE FOR THE DIFFERENT GROUPS

The principal endpoint will be assessed at the inclusion visit and during the follow-up visits at 3 and 6 months. The secondary endpoints will be assessed at the follow-up visits at 3 and 6 months.

## VISIT V1 - INCLUSION VISIT

The investigator will inform parents of potentially eligible minor patients and will invite their child to take part in the cohort study aiming to assess changes in diabetes control over a 6-month period (Information leaflet 1_ APPENDICES 8 and 9). Adult patients will be informed by the investigator directly.

Non-objection by the parents and/or adolescents will be documented in the patient’s medical record (date on which the information was provided, objection expressed or not, and signature of the person in charge of the visit).

Clinical examination

After verifying the eligibility criteria and non-objection to participation in the study, the investigator will collect the medical history and clinical information usually taken into account in the management of diabetic patients:

- medical history
- history of psychiatric disorders
- date of diabetes diagnosis
- current treatment regimen and insulin analogue injection times

Laboratory tests

Glycated haemoglobin (HbA1c) levels will be measured according to the method used at Centre Hospitalier de Necker.

Randomisation

- Patients randomised to the “text messaging” investigational arm: a second information leaflet (IL2- APPENDICES 10 and 11) on the study objectives and text messaging intervention procedures will be given to the parents and/or young patients. If patients refuse the text messaging intervention, the patients will receive conventional follow-up. Non-objection by the parents and/or adolescents to the text messaging intervention will also be documented in the patient’s medical record (date on which the information was provided, objection expressed or not, and signature of the person in charge of the visit).
- Patients randomised to the “standard management” control arm will receive their usual care.
- Completion of the quality of life questionnaire for all patients

At the end of the visit, the investigator will send the information sheet for centralised data entry.

## FOLLOW-UP VISITS at 3 and 6 months (M3 and M6)

The following procedures will be performed during these visits:

- Clinical examination
- Blood samples for laboratory work-up (assay of HbA1c level)
- Collection of the capillary blood glucose diary
- Distribution of a second capillary blood glucose diary
- Completion of the quality of life questionnaire for all adolescents
- Collection of any adverse events
- Satisfaction survey for patients randomised to the text messaging arm at M6.

These visits will be held with the doctor who included the patient in the study, and at the usual treatment centre.

At the end of the visit, the investigator will send the information sheet for centralised data entry.

## Summary table of the study time-line

|  | Inclusion | M3 | M6 |
| --- | --- | --- | --- |
| Eligibility | X |  |  |
| Information | X |  |  |
| Non-objection | X |  |  |
| Randomisation | X |  |  |
| Clinical form to be completed | X | X | X |
| Clinical examination | X | X | X |
| Assay of HbA1c level | X | X | X |
| Distribution of blood glucose monitoring diary | X | X |  |
| Text message sent | X | X | X |
| Collection of blood glucose diary |  | X | X |
| Quality of life questionnaire | X | X | X |
| Satisfaction survey (text messaging arm) |  |  | X |

Table 2: Summary table of the study time-line

## WITHDRAWAL FROM THE TRIAL AND PREMATURE WITHDRAWAL

The participants will leave the study after the 6-month follow-up period.

The patient, or person with legal authority, may withdraw their participation in the study at any time, without their decision compromising their continued treatment, quality of care or relationship with their doctor in any way.

Any patients erroneously included and not fulfilling the inclusion and exclusion criteria will be prematurely withdrawn from the trial. Other deviations from the protocol will not be considered as study withdrawals.

The investigator should document the reasons for premature withdrawal as thoroughly as possible. Study withdrawals should notably be related to the following reasons:

- Refusal by the subject or his/her parents to continue taking part in the trial
- Patient included erroneously
- Patient lost to follow-up

If a participant does not attend the follow-up visits, the investigator responsible for the patient’s care should contact the patient to determine his/her condition at the time of withdrawal from the study. If it is impossible to contact the patient, s/he will be considered lost to follow-up at the date of the last visit.

Patients withdrawn from the trial cannot be re-included in the study. Their inclusion number will not be re-used.

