# **SYNOPSIS**

| Title | Impact of Mobile Phone Short Text Messages on the Glycaemic Control of Adolescents With Poorly Controlled Type 1 Diabetes. |
| --- | --- |
| Coordinating Investigator | [name] |
| Investigating Centre | Paediatric Endocrinology Department, Hôpital Necker |
| Type of standard care assessed | Text message sent to adolescents reminding them to administer their insulin injection |
| Study duration | 1 year |
| Patient follow-up | 6 months |
| Target population | Adolescents aged between 12 and 20 years inclusive, with inadequately controlled type 1 diabetes |
| Study objective | The primary objective of this study is to assess whether intervention by sending a text message to adolescents with inadequately controlled type 1 diabetes reduces the HbA1c level by 1% at 6 months.  Secondary objectives:   - Measurement of compliance at 3 and 6 months. - Measurement of quality of life at 3 and 6 months - Changes in HbA1c level at 3 months |
| Methodology | Prospective randomised single-centre interventional standard care study. Randomisation as per the Zelen method. |
| Planned number of centres | 1 |
| Planned number of patients | 100 subjects will be included  50 patients in group G1 = Standard management  50 patients in group G2 = Text messaging |
| Selection criteria | Inclusion criteria:   - aged between 12 and 20 years inclusive - type 1 diabetes - diagnosed more than 6 months previously - HbA1c level at enrolment greater than or equal to 8.5% - for minors: no objection by a person with parental authority - for adults: no objection by the patient - previous medical examination (Art. L.1121-11 of the French Public Health Code) - able to be followed up for 6 months following inclusion. - patient registered with or covered by a health insurance scheme - adolescents with a mobile phone able to receive text messages (SMS)   Exclusion criteria:   - aged under 12 years or over 21 years - with a HbA1C level at enrolment < 8.5%. - pregnancy - serious psychiatric comorbidity, such as serious personality disorder or psychosis. - patient and/or parents unable to understand or speak French, hence unable to understand the non-objection form. |
| Criteria for premature withdrawal | - withdrawal of consent - decision by the patient or parents to no longer be followed up in the study |

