| Study implementation | Adolescents with type 1 diabetes whose current glycated haemoglobin level is greater than or equal to 8.5% are included and randomised to two groups, then followed up for 6 months:   - patients with standard follow-up (G1), - patients with standard follow-up and receiving text messages (SMS) (G2).   V0- Inclusion visit   - Verification of eligibility criteria - Invitation to take part in the study. - Collection of the non-objection form for participation in a cohort on compliance (IL1) - Randomisation. - Only adolescents randomised to group G2 are informed that they will receive text messages (SMS) (Zelen method). - Collection of the non-objection form for participation in the text messaging (SMS) study if the patient is randomised to the investigational arm (IL2) - Inclusion - Clinical examination - Blood sample: assay of HbA1c level - Completion of quality of life questionnaire - Completion of inclusion form   M3 – 3-month visit   - Clinical examination - Blood samples for laboratory work-up (assay of HbA1c level) - Completion of M3 follow-up form - Completion of quality of life questionnaire - Collection of blood glucose monitoring diary and distribution of a second diary   M6 – 6-month visit:   - Clinical examination - Blood samples for laboratory work-up (assay of HbA1c level) - Completion of M6 follow-up form. - Collection of capillary blood glucose diary distributed at M3. - Completion of quality of life questionnaire - Satisfaction survey for patients randomised to the text messaging arm   Text messaging characteristics:   - A text message will be sent every day. - At the usual insulin injection times based on the patient’s personal therapeutic regimen. - Example of message content:   *“Remember to administer your slow-acting insulin injection.”*  *“You are about to have your meal; remember to administer your rapid-acting insulin injection (or bolus - if a pump is used).”*  *“Remember to administer your mixed insulin injection.”* |
| Primary and secondary endpoints | Primary endpoint   - HbA1c level at 6 months   Secondary endpoints   - HbA1c level at 3 months - Measurement of compliance at M3 and M6: blood glucose monitoring diary - Inclusion, M3 and M6 quality of life questionnaire. - Satisfaction survey for patients randomised to the text messaging arm |

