## INCLUSION CRITERIA

- aged 12-20 years
- child with type 1 diabetes
- type 1 diabetes diagnosed more than 6 months previously, HbA1c level > or equal to 8.5% at inclusion
- For minors: Non-objection by a parent and the patient
- For adults: Non-objection by the patient
- Children having had a previous medical examination (Art. L.1121-11 of the French Public Health Code)
- Able to be followed up for 6 months following inclusion.
- Patient registered with or covered by a health insurance scheme
- Adolescents with a mobile phone able to receive text messages (SMS)

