# STATISTICAL CONSIDERATIONS

## Rationale for the sample size

Based on the results of the Hvidore study (Holl RW Eur J Pediatr 2003), we assume that the HbA1c level will follow a normal distribution, with a standard deviation of 1.6. The sample size necessary was calculated to evidence a difference in HbA1c level between the 2 “standard management” and “text messaging” groups of at least 1% after a 6-month follow-up period. Taking into account a type I error of 5% and 80% power, 41 subjects per group, i.e. 82 subjects in total, will need to be included and randomised.

To take into account a potential rate of refusal to take part in the “text messaging” arm, of approximately 10%, the sample size necessary was increased by 20%, i.e. 50 subjects per group, 100 subjects in total (Zelen, Stat med 1990).

Children who withdraw their consent, after being randomised to the “text messaging” arm will be followed up under the same conditions as those in the “standard management” group.

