## Description of planned statistical methods, including the planned interim analysis schedule

The statistical analysis will be carried out using SAS software, under the supervision of [name] (Paris Centre CRU - Cochin-Necker). The statistical analysis will be carried out at the end of data collection, data entry and data consistency checks.

A descriptive analysis of the characteristics of the children included in each group will be performed first of all. Quantitative data are expressed as the mean ± standard deviation or median and range, and as the sample size and percentage for qualitative data.

The primary endpoint and secondary endpoints will be analysed on an intention-to-treat basis, i.e. all randomised patients will be analysed in their randomisation arm, irrespective of the intervention received. All tests used will be two-sided, with a 5% significance level.

*Main analysis*

The HbA1c level after the 6-month follow-up period will be compared between the “text messaging” and control groups using Student’s *t*-test.

*Secondary analyses*

The HbA1c level after the 3-month follow-up period will be compared between the “text messaging” and control groups using Student’s *t*-test.

For all secondary endpoints, satisfaction and compliance, two means will be compared using Student’s *t*-test or a Wilcoxon test if necessary. The percentages will be compared using the Pearson Chi-2 test or Fisher’s exact method, if necessary.

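### Section 5.4 withdraws randomised patients later found ineligible, which conflicts in effect with the intention-to-treat analysis in 12.2 and could remove patients unevenly between arms

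*Protocol*

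**What the plan says.** Protocol section 5.4 (withdrawal from the trial) states: "Any patients erroneously included and not fulfilling the inclusion and exclusion criteria will be prematurely withdrawn from the trial". The next sentence adds: "Other deviations from the protocol will not be considered as study withdrawals". Ineligibility is therefore the one protocol deviation that leads to withdrawal. The section lists erroneous inclusion as a withdrawal reason beside refusal and loss to follow-up, and bars re-inclusion. It does not say whether HbA1c at M3 and M6 is still collected.

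Section 12.2 sets an intention-to-treat analysis in which "all randomised patients will be analysed in their randomisation arm, irrespective of the intervention received". For the main analysis, "The HbA1c level after the 6-month follow-up period will be compared between the “text messaging” and control groups" by Student's t-test, which needs a 6-month value from each patient.

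Section 12.1 does deal with text-arm patients who withdraw consent to texting: they "will be followed up under the same conditions as those in the" control group. No matching sentence exists for patients found ineligible.

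On the order of steps at the inclusion visit, the synopsis puts "Blood sample: assay of HbA1c level" after randomisation and after the second non-objection step of the text arm. Section 5.2 puts laboratory tests before randomisation. Neither says that the HbA1c result must be in hand before a patient is randomised.

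**The concern.** An intention-to-treat analysis protects the comparison only if outcomes are sought from everyone randomised. A rule that ends participation after randomisation, for a reason other than the patient's own wish, works against that. An investigator who follows 5.4 as written would stop study collection of the primary endpoint for these patients. A statistical analysis plan can define analysis populations, but it cannot reliably recover values that investigators were told to stop collecting.

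The second worry is differential removal. The trial is open-label (section 4.1), so the person who judges that an inclusion was erroneous can know the arm. Some grounds for that judgement may also come to light more easily in the text arm. If removal depended on arm, the randomised comparison of 6-month HbA1c could be biased.

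**Working it through.** **1. The two rules side by side.** Section 5.4 governs participation and does not define the analysis set. Section 12.2 defines the analysis set and does not mention 5.4. The conflict is one of consequence: withdrawal leads to no study M6 HbA1c, and so to no contribution to the t-test. Nothing in the protocol reconciles them.

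**2. Could removal differ by arm?**
- *Phone criterion.* Section 6.1 requires a phone that can receive SMS. The inclusion form (Appendix 3, item 7) has a field for the number only if the patient is in the text arm, and section 3 says that control patients receive no texts. A phone that never met the criterion could show up in the text arm and would probably go unnoticed in the control arm. Section 9.1.1 speaks of forwarding telephone details for all patients, unlike section 3, but with no texts sent to controls a fault would still not surface there.
- *HbA1c criterion.* Every patient has the same baseline assay. If its result arrives after randomisation, a value below 8.5% is acted on with the arm known. The grounds are the same in both arms, but the decision is not blind.

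**3. The protocol's sample size (12.1).** Inputs: difference 1, SD 1.6, two-sided 5%, power 80%.
- n per arm = 2 × [1.6 × (1.960 + 0.842)]² / 1² = 40.19, rounded up to 41. This matches.
- Inflation: 41 × 1.2 = 49.2, given as 50 per arm. The stated reason is refusal of texting, and no allowance is named for ineligible patients.

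**4. Power if all are kept.** With 10% refusal (12.1), and assuming that refusers gain nothing, the intention-to-treat difference is 1 × 0.9 = 0.9. The standard error is 1.6 × √(1/50 + 1/50) = 0.32. Power = Φ(0.9/0.32 − 1.96) = Φ(0.85) = 80.3%, or 79.5% with the noncentral t.

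**5. Loss of numbers only.** If k patients leave the text arm alone (k is assumed), the standard error is 1.6 × √(1/50 + 1/(50 − k)):

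| k removed | Power, normal | Power, t |
|---|---|---|
| 0 | 80.3% | 79.5% |
| 1 | 79.9% | 79.1% |
| 2 | 79.5% | 78.7% |
| 3 | 79.1% | 78.2% |
| 5 | 78.2% | 77.3% |

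The cost of 1 to 5 removals is about 0.4 to 2 points.

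**6. Shift in the arm mean.** If a share f of one arm is removed and those patients differ from the rest by g HbA1c points, the arm mean moves by f × g. For 5 of 50 and g = 1, that is 0.10 × 1 = 0.10, one tenth of the planned difference. Over assumed ranges of f from 2% to 10% and g from 0.5 to 1.5, the shift runs from 0.01 to 0.15. If removed text-arm patients would have had higher values, the shift favours texting; if lower, it goes against texting.

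**7. Equal removal.** If both arms lose the same kind and share of patients, the shift is 0. With 2%, 5% or 10% lost from each arm, power (normal) is 79.5%, 78.3% or 76.1%.

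**The case against.** Several points on the other side carry weight.

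*The rule is arm-neutral.* A reader might infer that 5.4 will remove patients unevenly. The documents do not show this. No arm is named, and section 5.2 has eligibility verified for everyone before randomisation. A baseline HbA1c below 8.5% is found on the same assay in both arms and cannot be affected by texting. A phone that fails later is not an erroneous inclusion; only one that never met the criterion would count, and no rate is given. Uneven removal therefore stands as a possibility and no more.

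*The order of steps may be only a list.* The synopsis also puts eligibility verification first. A reader might infer that patients qualify on an older HbA1c and are then overturned by the baseline value. The protocol describes no such two-value scheme: section 6.1 requires the level at inclusion, and the form has one field for it. What stands is that the two sections differ and should agree.

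*Consent.* The synopsis gives "withdrawal of consent" as a criterion for premature withdrawal, and a reader might see a contradiction with 12.1. It largely dissolves. There are two non-objections, one to the cohort and one to texting (section 4.4.2). The flow chart and sections 5.2 and 12.1 keep those who refuse texting in follow-up, and the M3 and M6 forms record STOP messages beside HbA1c.

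*Data may exist anyway.* HbA1c is monitored quarterly and source data are the medical records, so values might be retrieved. But nothing in 5.4 says they will be, and the section groups these patients with those who refused or were lost.

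**Conclusion.** The conflict between 5.4 and 12.2 holds. It is a stated rule that, followed as written, ends study collection of the primary endpoint for some randomised patients; it is more than a detail left for an analysis plan. It should be corrected.

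Its likely effect is modest. The loss of power is about 0.4 to 2 points for 1 to 5 text-arm removals, and a shift of about 0.1 needs 5 of 50 removed from one arm only with a 1-point difference. These counts and gaps are assumptions, as is the 0.9 difference, which rests on the protocol's 10% refusal with no benefit in refusers. The documents give no ineligibility rate and nothing that fixes the direction of bias. They support saying that the rule can remove patients unevenly, not that it does.

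**What to change.** Change section 5.4 to something like: *Patients found after randomisation not to meet the eligibility criteria are recorded as protocol deviations. Unless they object, they remain in follow-up, their HbA1c at M3 and M6 is recorded, and they are analysed in their randomised arm.* Confine any exclusion of such patients to a sensitivity analysis, based on pre-randomisation data and judged blind to arm. The right to withdraw at any time in sections 5.4 and 6.3 stays as it is.

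Reconcile the synopsis with section 5.2, and state that the qualifying HbA1c result is available before randomisation.

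The cost is protocol wording. HbA1c is already monitored quarterly in both arms (section 3), so no extra sampling is needed. The downside is that a few ineligible patients stay in the main analysis and may slightly dilute the effect.

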## DISCONTINUATION OF THE STUDY

The decision may be made to discontinue the whole study prematurely due to:

- inadequate recruitment
- unresolved technical problems
- desire expressed by the investigators
- repeated and unjustified protocol violations

# STUDY POPULATION

In this study, patients aged 12-20 years are referred to as “adolescents”.

## INCLUSION CRITERIA

- aged 12-20 years
- child with type 1 diabetes
- type 1 diabetes diagnosed more than 6 months previously, HbA1c level > or equal to 8.5% at inclusion
- For minors: Non-objection by a parent and the patient
- For adults: Non-objection by the patient
- Children having had a previous medical examination (Art. L.1121-11 of the French Public Health Code)
- Able to be followed up for 6 months following inclusion.
- Patient registered with or covered by a health insurance scheme
- Adolescents with a mobile phone able to receive text messages (SMS)

## EXCLUSION CRITERIA

- Aged strictly below 12 years or 21 years or over
- Child with non-insulin-dependent diabetes.
- Pregnancy (declared)
- Serious psychiatric comorbidity, such as serious personality disorder or psychosis.
- Patient and/or parents unable to understand or speak French, hence unable to understand the non-objection form.

## STUDY WITHDRAWAL CRITERIA

The decision by the patient or a parent to no longer be followed up in the study represents a study withdrawal criterion.

# PATIENT INFORMATION PROCEDURES

In compliance with French law no. 2004-806 of 9 August 2004 on public health policy, the investigator is obliged to inform patients prior to their participation in a study aiming to assess standard care.

## Patient information

In compliance with Article R. 1121-3 of the French Public Health Code, persons who take part in a study are informed via a written document, submitted to the relevant ethics committee beforehand. When the patient is being included in the study, the patient or his/her representative will be given information on the study verbally or in writing, via the information leaflet distributed by the doctor.

When the study has ended, the person taking part in the study may be notified of the overall results of the study, in accordance with the procedures stated in the information leaflet.

## (Non)-objection by the patient or his/her representative to participation in the study

In the context of studies aiming to assess standard care, the patient has the option to object to participation in the study. This is stated in the information document stipulated in Article R1121-3 of the French Public Health Code. (refer to the French decree of 9 March 2007 laying down the contents of the application for an opinion from the Ethics Committee for studies aiming to assess standard care, mentioned in paragraph 2°, Article L. 1121-1 of the French Public Health Code).

Patient information and non-objection should be documented and dated in the medical record. If the patient objects to be included in the study, s/he will continue to receive standard management. Non-objection by only one of the two parents should be documented for a standard care protocol.

Non-objection by the parents and adolescents will be documented in the patient’s medical record: date on which the information was provided, objection expressed or not, and signature of the person in charge of the visit.

